### Statistical procedures

#### Sample size

The sample size was calculated on the basis of a significant reduction in the amount of calories ingested after a single 20-minute session of active tDCS (*F*_1,8_ = 8.4, *p* = 0.02, ηp^2^ = 0.5) [12]. Three types of analysis were performed using G*Power 3.1.9.2® software, considering a power of 80% and an α of 0.05, as follows: effect size (*f*) = 1.0, 10 subjects; effect size (*f*) = 0.8, 12 subjects; and effect size (*f*) = 0.6, 20 subjects. In another study, a 14.2% reduction in the amount of calories ingested was observed after 8 consecutive days of active tDCS sessions. The authors considered a medium effect size (*d*) > 1.09 as sufficient for their findings [13]. Following these assumptions, a total of at least ten subjects would be required in each group to detect a medium-sized effect. Because of possible dropouts, we will include an additional 40% of participants in this study.

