**Methods/design:**

Overweight or obese adults between 20 and 50 years of age with stable weight over the last 4 months will be selected for a 4-week randomized clinical trial of fixed-dose tDCS (20 sessions; 5 consecutive weekdays/wk, 2 mA, 20 minutes) over the right dorsolateral prefrontal cortex associated with a weight loss diet. The subjects will be randomly assigned in a 1:1 ratio and stratified by sex to active tDCS + diet or sham tDCS + diet. The study will be conducted at the Endocrine and Metabolism Unit of the Hospital de Clínicas de Porto Alegre, Brazil. The primary outcome is weight loss. Energy and macronutrient consumption, as well as adherence to the diet, will be assessed using 3-day weighed dietary records. Changes in blood glucose and plasma insulin will be assessed, and participants will complete self-report questionnaires to assess changes in mood and food behavior. All analyses will be done on a per-protocol and intention-to-treat basis.

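### Ten per group is said to detect a medium-sized effect at 80% power, but the inputs are very large calorie-intake effects, the quoted d = 1.09 reaches 80% only under favourable correlation assumptions, and weight is not sized at all

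*Protocol article*

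**What the plan says.** All of the sizing is in the Sample size section of the protocol article.

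- Source: "The sample size was calculated on the basis of a significant reduction in the amount of calories ingested after a single 20-minute session". The figures come from a cited study with F(1,8) = 8.4, p = 0.02 and partial eta squared 0.5.
- Three G*Power results. The largest effect comes first: "considering a power of 80% and an α of 0.05, as follows: effect size (*f*) = 1.0, 10 subjects". For the middle one the article gives "effect size (*f*) = 0.8, 12 subjects", and for the smallest it gives "effect size (*f*) = 0.6, 20 subjects". Test family, sidedness, number of measurements and correlation are not given.
- A second cited study, with a 14.2% reduction in calories over eight days, supplies d > 1.09, described there as medium.
- Conclusion: "Following these assumptions, a total of at least ten subjects would be required in each group to detect a medium-sized effect". A further 40% is added for dropouts.

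The Abstract says: "The primary outcome is weight loss". The Outcomes section has a longer primary list: body weight, BMI, and energy and macronutrient intake. The Data analysis section plans a GEE with group, time and group-by-time terms.

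**The concern.** The concluding sentence tells the reader what the trial can detect, and that description does not fit the numbers before it. None of the effects entered is medium in the usual sense, and the one quoted just before the conclusion, d = 1.09, is smaller than the smallest f for which a sample size is listed (f = 0.6, d = 1.2). Nothing in the paragraph is expressed in weight.

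At stake is how a null result is read. If the article stands, a reader may take a non-significant weight comparison as evidence against a moderate benefit, when the trial has good power only for a very large one. Nor can the reader tell what difference in kilograms the trial could find.

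**Working it through.** **Inputs.** From the Sample size section: alpha 0.05, power 80%, f = 1.0, 0.8 and 0.6, d = 1.09, ten per group, plus 40%. Enrolment is 20 × 1.4 = 28, which agrees with the Randomization section (2 × 6 + 4 × 4 = 28), so 14 per arm. Tests are taken as two-sided. For two equal groups d = 2f, so f = 1.0, 0.8, 0.6 are d = 2.0, 1.6, 1.2, and d = 1.09 is f = 0.545.

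**Check of the source.** Partial eta squared = 8.4/(8.4 + 8) = 0.512 and p = 0.020. With eta squared 0.5, f = √(0.5/0.5) = 1.0. The inputs are consistent.

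**Reproducing 10, 12 and 20.** Repeated-measures ANOVA, between-groups factor, m = 2 measurements, correlation r = 0.5 (m and r are my assumptions): λ = f²·N·m/(1 + (m − 1)r) = f²·N·4/3, with 1 and N − 2 df, smallest even N with power of at least 80%.

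- f = 1.0, N = 10: λ = 13.3, power 89.1%
- f = 0.8, N = 12: λ = 10.2, power 82.2%
- f = 0.6, N = 20: λ = 9.6, power 83.4% (N = 18 gives 78.8%)

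All three totals match. Ten per group is therefore the f = 0.6 result.

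**Power with ten per group under other tests.**

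- Two-sample t: noncentrality d√(n/2), 2n − 2 df.
- Change score: replace d by d/√(2(1 − r)). At r = 0.5 the divisor is 1, so the result equals the t test.
- ANCOVA on baseline: replace d by d/√(1 − r²), 2n − 3 df.

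| Effect | t test, or change score at r = 0.5 | ANCOVA, r = 0.5 | RM between-factor, r = 0.5 |
|---|---|---|---|
| d = 2.0 (f = 1.0) | 98.8% | 99.8% | 99.8% |
| d = 1.6 (f = 0.8) | 92.2% | 97.3% | 97.4% |
| d = 1.2 (f = 0.6) | 71.8% | 83.1% | 83.4% |
| d = 1.09 | 63.5% | 75.6% | 75.9% |
| d = 0.5 | 18.5% | 23.0% | 23.1% |

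For 80% power at d = 1.09 the t test needs 15 per group and the between-factor routine needs 22 in total. At r = 0.7 and d = 1.09, ten per group gives 84.5% by change score and 89.5% by ANCOVA. The 80% line is crossed at r of about 0.66 and 0.57 respectively. With all 28 retained, d = 1.09 gives 79.3% by t test and 89% by ANCOVA or the between-factor routine at r = 0.5. For d = 0.5 the t test needs 64 per group.

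**What the matching routine tests.** The between-factor test compares the arms on the average of baseline and follow-up. Under randomisation the expected baseline difference is zero, so a follow-up difference of f = 0.6 averages to f = 0.3. Then λ = 0.09 × 20 × 4/3 = 2.4 and power is 31%. A group-by-time question at two time points is the change comparison, with 71.8% at f = 0.6 and r = 0.5.

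**Detectable difference at 80% (unadjusted t).** d = 1.33 with 10 per arm (1.325 before rounding up) and 1.10 with 14. With ANCOVA at r = 0.5 these become 1.15 and 0.95. Assume, for illustration, an SD of 4-week weight change of 1.5 to 2.5 kg and take d in units of that SD. Fourteen per arm then detects 1.10 × 1.5 = 1.65 kg to 1.10 × 2.5 = 2.75 kg, and ten per arm 1.33 × 1.5 = 2.0 kg to 1.33 × 2.5 = 3.3 kg. The diet target of 3% is 0.03 × 85 = 2.55 kg at an assumed 85 kg.

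**The case against.** The strongest reply is that the figures are not miscalculated. The totals 10, 12 and 20 come back exactly from a standard routine, and ten per group exceeds 80% at f = 1.0 and 0.8 even by an unadjusted two-sided t test. At f = 0.6 the answer turns on a test and a correlation that the article does not state: 72% by change score at r = 0.5, 83% by ANCOVA at the same r. This stands. A reader might infer that ten per group fails for the plan's own listed effect sizes; the document does not support that.

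The routine is also inferred. ANCOVA at r = 0.5 (9, 12, 19) and a one-sided t test (8, 12, 20) come within two subjects of the stated totals, and a condensed article may leave such settings to the full protocol. So the mismatch with the group-by-time question is conditional on that routine having been used. Sidedness is unstated too, but a one-sided t test at d = 1.09 with ten per group still gives only 75.8%. The between-factor routine would reach 82% at r = 0.3, but only by supposing the arms already differ at baseline. Weekly weights in the GEE may add precision, by an amount that the article gives no basis to quantify.

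A reader might also infer that the sizing ignores the primary outcome altogether. That goes too far, since the Outcomes section lists energy intake as primary. What remains is that weight and BMI have no sizing, and that the f inputs come from one session rather than four weeks on a diet.

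Finally, the medium label on d > 1.09 is attributed to a cited study. The protocol nevertheless adopts it in its own conclusion.

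**Conclusion.** The point holds in this form. Describing the detectable effect as medium is wrong: every input is above d = 0.8, and at d = 0.5 ten per group has 19% to 23% power. At d = 1.09 ten per group gives about 63% to 76% with correlation 0.5, short of 80%. A change or baseline-adjusted analysis reaches 80% only at a correlation above roughly 0.57 (ANCOVA) to 0.66 (change score). These figures assume two-sided 5% tests, two time points, equal arms and ten completers per arm. No weight or BMI difference is justified anywhere in the calculation.

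It is not shown that the G*Power arithmetic is wrong, nor that power falls short at f = 1.0 or 0.8. The shortfall at f = 0.6 and the mismatch with the group-by-time test depend on settings that are not stated. The kilogram figures are illustrations under an assumed SD and body weight.

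**What to change.** Rewrite the Sample size paragraph and leave enrolment at 28.

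1. Delete the medium-sized description.
2. Name the test used in G*Power, its sidedness, the number of measurements and the assumed correlation. If it was the between-factor test, replace it with the group-by-time or baseline-adjusted comparison that the GEE will make.
3. State that 80% power exists only for a large between-arm difference: unadjusted d of about 1.10 with 14 per arm, 1.33 with 10 per arm, and smaller with baseline adjustment under the stated correlation.
4. Give power at d = 1.09 under the same assumptions (unadjusted, 63% with 10 per arm and 79% with 14).
5. Say that the calculation rests on calorie intake. Add the detectable 4-week weight difference in kilograms under an assumed SD with its source, and say that the weight result will be interpreted through its confidence interval.

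The cost is wording and a short recalculation, with no extra participants and no design change. The stated power becomes less favourable.

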#### Data analysis

To compare the participants’ baseline characteristics, Student’s *t* test and the chi-square test will be used as appropriate. The results will be expressed as mean ± SD, mean (95% CIs), or the number of patients with the characteristic (percent). The Shapiro-Wilk test will be used to verify data normality; variables with non-Gaussian distribution, such as insulin and the HOMA index, will be logarithmically transformed before analysis when necessary. The aRMR will be performed using logarithmically transformed data, as recommended by Kaiyala and Schwartz [40].

The effects of tDCS between groups over time will be analyzed using the generalized estimating equation (GEE), including tDCS group, time, and the group- and subgroup-by-time interaction as predictors. All GEE models will be followed by a Bonferroni post hoc analysis and the least significant difference test to identify significant differences detected by the GEE. Gamma distribution with log link function will be used for variables with non-Gaussian distribution. After treatment of the first ten participants, an interim security analysis was planned, and the trial may be stopped prematurely because of safety concerns, such as severe psychiatric and neurologic reactions. The outcomes will be presented as *p* values for the included factors and estimated marginal means, with corresponding 95% CIs for each tDCS group at each time point. A *p* value < 0.05 will be considered statistically significant. IBM SPSS Statistics version 19.0 statistical software (IBM, Armonk, NY, USA) will be used for the analyses.

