### Outcomes

The primary outcomes will be reductions in body weight and BMI from baseline and reduction or maintenance of the prescribed energy and macronutrient intake during the 4-week intervention. The secondary outcomes will be reduced hunger, desire to eat, and food craving scores compared with baseline; reductions in fasting and postprandial responses of plasma glucose, insulin, GA, hunger hormones such as ghrelin; and an increase in the blood levels of hormones that participate in the regulation of satiety, such as PYY_3–36,_ GLP-1, and PP [47]. These hormones will be measured to understand mechanisms behind a possible effect of tDCS in weight, desire to eat, food cravings, or glycemic control and variability.

The exploratory outcomes will include the number of participants achieving a 3% reduction or more in body weight compared with baseline; improvements in insulin sensitivity and β-cell function compared with baseline; changes in body composition, such as reduced waist and hip circumferences and reduced body fat mass, compared with baseline; changes in glycemic variability, such as reduced MAGE compared with baseline; changes in depression and anxiety scores compared with baseline; and acute changes in subjective feelings of desire to eat, mood, and attention between pre- and post-tDCS sessions.

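### Bonferroni and unadjusted LSD tests are both prescribed after every GEE model with no rule on which governs, and the listed results omit the active-minus-sham difference with its interval

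*Protocol article*

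**What the plan says.** All of the analysis text is in the protocol article, section Data analysis. The stated purpose of the model is a comparison of the arms over time by GEE. Its terms are given as: "including tDCS group, time, and the group- and subgroup-by-time interaction as predictors". The post hoc step is: "All GEE models will be followed by a Bonferroni post hoc analysis and the least significant difference test to identify significant differences". That sentence closes by tying these differences to what the GEE has found. The threshold is: "A *p* value < 0.05 will be considered statistically significant". For reporting, the section lists factor p values and, beside them, "estimated marginal means, with corresponding 95% CIs for each tDCS group at each time point".

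The Outcomes section words the targets as changes from baseline, for example: "The secondary outcomes will be reduced hunger, desire to eat, and food craving scores compared with baseline". The last paragraph of the Background states a between-arm hypothesis: better diet adherence, and hence greater weight loss, with active than with sham stimulation.

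**The concern.** Two problems sit in the same paragraph.

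- **Conflicting rules.** Bonferroni and LSD are alternative rules for the same set of pairwise comparisons. Prescribing both, with a single 0.05 threshold and no order of precedence, gives two verdicts on any contrast that falls between their cut-offs. The analyst can then choose which verdict to report once the results are known.
- **Per-arm results.** The listed results are factor p values and a mean with an interval for each arm at each visit. Pairwise testing of such means includes baseline-to-week-4 tests within each arm. Both arms follow a hypocaloric diet, so these tests reflect the diet as well as any stimulation effect. A report that the active arm changed significantly and the sham arm did not could be taken as evidence for tDCS without being a comparison of the arms. The size of the between-arm effect, with its uncertainty, would not be in the listed output.

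**Working it through.** **Planned size.** The Sample size section requires ten per group plus 40%: 10 × 1.4 = 14 per arm. The Randomization section gives 2 × 6 + 4 × 4 = 28 in total, again 14 per arm. No figure in the plan is disputed on this point.

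**Number of pairs.** With 2 arms and T visits there are 2T cells and K = T(2T − 1) pairs. The visits per model are not stated. The values below are assumptions taken from the schedule.

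| Visits T | Example from the schedule | Pairs K | LSD cut-off | Bonferroni cut-off 0.05/K |
|---|---|---|---|---|
| 2 | measures at baseline and end of treatment | 6 | 0.05 | 0.0083 |
| 3 | the three dietary-record periods | 15 | 0.05 | 0.0033 |
| 5 | baseline and four weekly weights | 45 | 0.05 | 0.0011 |
| 7 | the same plus 3 and 6 months | 91 | 0.05 | 0.00055 |

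Any raw p between the last two columns is significant under one rule and not under the other.

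**Error rates under a full null.** Trials were simulated with 14 per arm, no group or time effect, and within-person correlation 0.5 (assumed). Each pair of cell means was tested by estimate divided by standard error. Two references were used: a t reference with unbiased variance (lower figures) and a normal reference with uncorrected robust variance (upper figures). The table gives the chance of at least one flagged pair.

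| Use of the post hoc tests | 2 visits | 3 visits |
|---|---|---|
| LSD, all pairs, no gate | about 19–28% | about 37–49% |
| Bonferroni, all pairs | about 4–9% | about 4–12% |
| LSD, same-visit active versus sham only | about 9–13% | about 13–18% |
| LSD, only after a significant group-by-time term | about 4–6% | about 4–8% |

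As a check on the third row, two independent tests would give 1 − 0.95² = 9.75%. The excess of Bonferroni over 5% appears only with the normal reference. It comes from small-sample variance bias, and the same bias accounts for part of the upper LSD figures.

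With more visits (t reference, correlation 0.5 to 0.9), ungated LSD over all pairs gives 59–63% at five visits and 75–80% at seven, against about 2–4% for Bonferroni. Same-visit LSD gives 11–18% and 13–23%.

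**Which row applies.** For weight, the full null is not realistic because both arms diet. Within-arm pairs will then tend to be significant for reasons unrelated to tDCS, and the same-visit row is the relevant one.

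**Within-arm reading.** Suppose both arms improve equally by 0.5 SD of the change score (assumed), with 14 per arm. A result significant in the active arm only then occurs in about 24% of trials, with no tDCS effect. Over assumed improvements of 0.3 to 1.0 SD the range is 6–24%.

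**The case against.** The strongest reply has four parts.

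1. *The between-arm effect is modelled and tested.* This stands. A reader might infer from the per-arm output that no between-arm effect is estimated, or that there is no valid between-arm test. The document does not support that. The model contains group and group-by-time terms, the group-by-time term carries the difference in change between arms, and its p value is to be reported. The choice between Bonferroni and LSD cannot alter that p value.
2. *The post hoc sentence refers to differences detected by the GEE, so the pairwise tests are gated.* This is a natural reading, and if the gate is the group-by-time term it removes most of the inflation. The section does not name the gating term, however. A significant time term, which is expected for weight because both arms diet, would open the gate without protecting the arm comparisons.
3. *The all-pairs rates are a worst case.* This stands in part. They count cross-arm, cross-visit pairs that nobody would report as a tDCS effect, and they assume the number of visits. The same-visit and gated rows are therefore given beside them.
4. *The named contrast and table layout belong in an analysis plan, and change from baseline merely defines the variable.* The Outcomes wording alone is indeed not a defect, and an unseen analysis plan may add the difference. But the article does not leave the post hoc procedure open: it states two incompatible ones. It also lists the results to be presented, and the main quantity is not on the list.

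**Conclusion.** The point holds in a limited form. The stated post hoc rule contradicts itself, and with two visits the contested zone is a raw p from 0.0083 to 0.05. The consequence depends on how LSD is read: about 19–28% false flags with two visits and 37–49% with three if ungated over all pairs; about 9–13% and 13–18% if limited to same-visit arm comparisons; about 4–8% if read only after a significant group-by-time term. These figures rest on 14 per arm, an assumed correlation of 0.5 and assumed visit counts.

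Separately, the active-minus-sham difference in change with its interval is absent from the listed results, although it is the quantity in the hypothesis. It would be wrong to conclude that the trial lacks a between-arm test. What is missing is one governing post hoc rule and an interval for the effect. Both should be corrected before the data are analysed.

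**What to change.** - Delete the LSD test and keep Bonferroni as the single post hoc procedure.
- For weight and the other efficacy outcomes, report as the main result the active-minus-sham difference in change from baseline to week 4, with 95% CI and p from the group-by-time contrast. Where the gamma model with log link is used, give the contrast on its ratio scale.
- Report the 3- and 6-month between-arm differences, where measured, as secondary.
- Keep the per-arm means with intervals, present within-arm changes as descriptive, and state that they are not used as evidence of a tDCS effect.

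The cost is a few sentences in the Data analysis section. No extra data are needed, since the contrast comes from the model already planned. The downside is that fewer pairwise results will be called significant.

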#### Eating behavior assessment

*Hunger throughout the day* will be self-reported at baseline and at the end of the study (in the morning while the patient is still fasting) using a 100-mm VAS consisting of six word-anchored questions adapted from Haber et al. [34]. The participants will recall the intensity of their hunger upon waking, before lunch, 3 hours after lunch, before supper, 3 hours after supper, and before bedtime.

*Subjective satiety and hunger* scores will be assessed at baseline and at the end of the 4-week intervention using a 7-point VAS described by Holt and Miller [35]. On this scale, the participants will rate their hunger at “this very moment.” The answers range from − 3 = “extremely hungry” to 0 = “no particular feeling”, to + 3 = “extremely full”.

An additional 100-mm VAS, consisting of four word-anchored questions (“yes, very much” to “not at all”), will be administered before and after the 4-week intervention to assess the *desire to eat* something fatty, salty, sweet, or savory (as previously described) [36, 37].

The Food Craving Inventory–Brazilian version (FCI-Br), consisting of 23 food items distributed in 3 dimensions (sweet foods, high-fat foods, and traditional meals), will be applied at baseline and at the end of the study. The validated FCI-Br [38] has been adapted to include important characteristics of Brazilian eating habits. Like the original version [39], this tool begins with the question, “Over the past month, how often have you experienced a craving for the food listed below?” Each of the foods listed is evaluated using a 5-point Likert scale ranging from 1 = never to 5 = almost every day. The total score for each FCI dimension is calculated by the sum of the scores for each related item.

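### The gamma/log-link rule for non-Gaussian variables cannot be applied to the −3 to +3 hunger/satiety scale, and the plan names no usable alternative for it

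*Protocol article*

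**What the plan says.** All the analysis rules are in the Data analysis section of the protocol article. Normality is to be tested: "The Shapiro-Wilk test will be used to verify data normality". The paragraph that opens with the baseline comparisons adds that "variables with non-Gaussian distribution, such as insulin and the HOMA index, will be logarithmically transformed before analysis when necessary". The next paragraph sets the method for treatment effects, "The effects of tDCS between groups over time will be analyzed using the generalized estimating equation (GEE"), and gives the distributional rule for those models: "Gamma distribution with log link function will be used for variables with non-Gaussian distribution". No sentence limits the gamma rule to particular variables or says how it relates to the log-transform rule.

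The Eating behavior assessment section describes the scales. Satiety and hunger "scores will be assessed at baseline and at the end of the 4-week intervention using a 7-point VAS", on which −3 is extreme hunger, 0 is neutral and +3 is extreme fullness. Hunger through the day is recorded "using a 100-mm VAS consisting of six word-anchored questions", and desire to eat on a similar 100-mm scale. The Mood assessment section gives the depression score a minimum of 0. The Outcomes section lists hunger and desire to eat as secondary outcomes, and depression scores as exploratory. The Glycemic homeostasis section repeats the hunger and satiety ratings at each blood draw of the liquid meal test.

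**The concern.** A rule stated for all non-Gaussian variables must work for every variable that may meet the condition. This one does not work for a scale centred on zero. An analyst who follows it would find that the model does not run, or would drop the scores it cannot take. On this scale the inadmissible scores are every hungry answer plus the neutral one, so exclusion would depend on the outcome itself and could distort the comparison of arms. The remaining course is to choose a different model after seeing the data, which a prespecified rule is meant to prevent.

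**Working it through.** The plan gives no figure to reproduce. The check covers which values the models admit, how likely the rule is to be triggered, and what happens when it is followed.

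**1. Admissible values.** The gamma density exists only for y > 0. With shape 2 its log-density is −∞ at −3, −∞ at 0 and −1 at 1. The scale's scores are −3, −2, −1, 0, 1, 2, 3, so 4 of 7 fall outside. With a log link the fitted mean is exp(linear predictor), which is always positive, so a group whose mean score is negative cannot be fitted.

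**2. The other stated remedy.** log(y) is undefined for y ≤ 0, so log transformation fails on the same four scores.

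**3. Is the rule likely to be triggered?** The Randomization section gives two blocks of six and four of four: 2 × 6 + 4 × 4 = 28 participants. I simulated 4,000 samples of 28 scores per setting, as normal values rounded to integers and cut at −3 and +3. The means (−1.5 to 0) and SDs (1 and 1.5) are assumptions. Shapiro-Wilk at 0.05 rejected in 44% (mean 0, SD 1.5) to nearly 100% (mean −1.5, SD 1) of samples.

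**4. Following the rule on the signed scale.** One dataset of 28 participants at two visits (56 records) was simulated with assumed negative group means; the four cell means were −1.07, −0.93, −0.64 and −0.57. Of the 56 scores, 49 were ≤ 0. The gamma/log-link GEE stopped with an error (invalid weights). Keeping positive scores only left 7 of 56 records.

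**5. Scales with a floor of 0.** The article prints 0 as the minimum for the depression score. For the 100-mm scales, 0 mm is inferred. In one simulated 0–100 dataset (assumed values), 4 of 56 scores were 0. The GEE still solved, because estimating equations need a positive mean rather than a gamma likelihood. Dropping the zeros moved the time coefficient from −0.258 to −0.103. The group-by-time coefficient stayed at −0.186, because the zeros happened to fall equally in the two arms. The result therefore depends on how zeros are handled, but this example shows no bias in the arm comparison.

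**6. Insulin and HOMA.** These are positive, so either rule can be fitted, but they target different quantities. Log transformation gives a ratio of geometric means (GMR) and gamma/log link a ratio of arithmetic means. For lognormal data the arithmetic ratio is GMR × exp[(s₁² − s₀²)/2], where s₀ and s₁ are the two groups' log-scale SDs. With GMR 0.85 (assumed):
- s₀ = s₁ = 0.5: 0.85 × exp(0) = 0.85.
- s₀ = 0.5, s₁ = 0.7: 0.85 × exp[(0.49 − 0.25)/2] = 0.85 × exp(0.12) = 0.958.

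**The case against.** The best reply is that the damage is narrow. The rule bites only if a variable is judged non-Gaussian, hunger is also measured on the 100-mm scale, and a model for each variable could be left to an analysis plan that is not shown. The first two points stand and limit the severity. The third does not remove the defect: the article is not silent but states a general rule that one of its own instruments cannot meet.

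Several stronger conclusions are tempting, and the document does not support them:

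- **That the 100-mm scales will usually be sent to the gamma model.** In 4,000 simulated samples of 28 per setting, means of 40 to 50 with SDs of 20 to 25 led to rejection in only 4% to 6%. Mean 30 with SD 25 gave 30%, and mean 20 with SD 20 gave 54%. The answer depends on floor effects that the article does not describe.
- **That 57% of the data would be lost.** Four of seven counts answer codes. The article gives no expected distribution of answers, and ratings are also taken after the test meal.
- **That the log-transform and gamma rules contradict each other.** The first sits in the paragraph that opens with baseline t tests and is qualified by necessity; the second sits in the GEE paragraph. They can be read as covering different analyses. But insulin and HOMA are named without restriction to baseline, so the text is ambiguous.
- **That gamma models would be fitted to logged values, and so fail for HOMA-IR below 1.** Nothing in the article combines the two rules in that way.
- **That the gamma rule should be deleted.** Craving scores are sums of items scored 1 to 5, and insulin, HOMA and hormone values are positive. Gamma with log link is admissible for all of them, and preferring log transformation there is a matter of taste.

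**Conclusion.** The point holds for the −3 to +3 scale: neither stated remedy for non-Gaussian variables can take scores of −3 to 0. That the rule cannot be applied there follows from the scale's definition and needs no assumption. How likely it is to be triggered rests on assumed score distributions, but rejection was frequent in every setting tried for the seven-point scale. Scales that can take the value 0 are affected more mildly, depending on how zeros are treated. For insulin and HOMA the defect is an unclear choice between two workable rules. The primary outcomes of weight, BMI and energy intake are positive and are not affected as raw values. Severity is minor to moderate, confined to secondary and exploratory outcomes.

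**What to change.** Amend the Data analysis section in three respects:

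1. Limit the gamma/log-link rule to outcomes that are strictly positive.
2. Analyse the −3 to +3 scale, and scales that can be 0 (the depression score and the 100-mm items), on the raw scale by identity-link GEE with robust standard errors. An ordinal model is an acceptable alternative for the seven-point scale.
3. State which single rule, log transformation or gamma with log link, governs the GEE for insulin and HOMA. If the log-transform sentence is meant only for the baseline t tests, say so.

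The cost is analysis wording only. No visit, measurement, sample size or treatment procedure changes. The choice should be recorded before outcome data are examined by arm.
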